## Abstract

**Background:**

High intensity and endurance exercises lead to exercise-induced oxidative stress (EIOS), exercise-induced muscle damage (EIMD), and inflammation, which are the influencing factors on muscle soreness, localized swelling, and sports performance decrease. Therefore, the purpose of this study is to determine the effectiveness of *Tribulus terrestris* (TT) as an herbal supplement with antioxidant and anti-inflammatory properties on the nutritional, oxidative, inflammatory, and anti-inflammatory status, as well as the sports performance of recreational runners.

**Methods/design:**

This study is a double-blind, randomized, placebo-controlled trial, which will be conducted among recreational runners of Tabriz stadiums, Iran. Thirty-four recreational runners will be selected, and participants will be assigned randomly to two groups: to receive 500 mg TT supplement or placebo capsules twice daily for 2 weeks. Both groups will do high-intensity interval training (HIIT) workouts during the study. Baseline and post-intervention body composition, muscle pain, and aerobic and anaerobic performance will be assessed. In addition, assessment of malondialdehyde (MDA), total antioxidant capacity (TAC), total oxidant status (TOS), superoxide dismutase (SOD), glutathione peroxidase (GPx), uric acid (UA), 8-iso-prostaglandin F2α (8-iso-PGF2α), protein carbonyl (PC), catalase (CAT), glutathione (GSH), nitric oxide (NO), high-sensitivity C-reactive protein (hs-CRP), interleukin-6 (IL-6), interleukin-10 (IL-10), tumor necrosis factor-alpha (TNF-α), creatine kinase (CK), myoglobin (MYO), lactate dehydrogenase (LDH), insulin-like growth factor-1 (IGF-1) irisin, cortisol, and brain-derived neurotrophic factor (BDNF) will be done during three blood samplings. Changes in oxidative stress, anti/inflammatory biomarkers, and sports performance will be assessed as primary outcomes.

**Discussion:**

This study will be the first to assess the potential effects of TT on recreational runners. Our results will contribute to the growing body of knowledge regarding TT supplementation on the nutritional, oxidative, inflammatory, and anti-inflammatory status and sports performance in recreational runners.

**Trial registration:**

Iranian Registry of Clinical Trials (www.irct.ir) (ID: IRCT20150205020965N8). Registration date: 13 February 2021.

**Supplementary Information:**

The online version contains supplementary material available at 10.1186/s13063-022-06630-0.

## Background

The World Health Organization indicates that regular physical activity is well-known for providing health benefits and preventing chronic and non-communicable diseases, including heart disease, stroke, diabetes, and several cancers [1]. Even so, several studies have proposed that intensive and unaccustomed exercises can lead to impaired muscle function, athletic performance, and recovery [2, 3]. High intensity and endurance exercises lead to an imbalance between oxidants and antioxidants in favor of the oxidants, defined as exercise-induced oxidative stress (EIOS) [4]. EIOS and the high level of reactive oxygen species can contribute to muscle damage [2, 4]. Besides, it should be noted that prolonged muscle contractions can result in a condition called exercise-induced muscle damage (EIMD). EIOS and EIMD are the influencing factors that result in muscle soreness, localized swelling, increased levels of creatine kinase (CK), lactate dehydrogenase (LDH), myoglobin (MYO), and inflammatory markers including C-reactive protein (CRP), interleukin 1 (IL-1), interleukin 6 (IL-6), and tumor necrosis factor-alpha (TNF-α) [3, 5],which lead to poor athletic performance. Considering the point that oxidative stress is the leading factor of the mentioned phenomenon, there is a growing interest in the use of antioxidant supplements by physically active individuals. Also, it seems that supplements with antioxidant and anti-inflammatory properties will provide more favorable effects. *Tribulus terrestris* (TT) is one of the herbal supplements with mentioned properties.

TT is a native plant of Iran classified in the family Zygophyllaceae [6, 7]. It can be found in a wide range of warm and humid regions such as the Mediterranean regions, Asia, Australia, Africa, and the warm areas of Europe [8] and contains a high concentration of active ingredients such as sterol saponins, flavonoids, tannins, terpenoids, phenol carboxylic acids, and alkaloids. The leaves, seeds, and fruits of TT are used for therapeutic purposes; however, studies indicate that the highest amount of TT's active ingredients is found in its fruit [6, 8]. According to existing studies, a variety of components in TT appear to contribute to its antioxidant capacity [9]. There may be a probable association between antioxidant activity and total saponin concentration of TT, according to Figueiredo *et al.’s* study [10]. Furthermore, Hammoda *et al.* found that the presence of di-p-coumaroylquinic acid derivatives would play a key role in the antioxidant activity of TT [11]. Ștefănescu *et al.* also credited TT’s antioxidant activity to its polyphenols and flavonoids [8]. Studies concentrating on the therapeutic effects of TT have assessed its potential effects on sexual enhancement [12], fertility [13], urinary tract stones [14, 15], diabetes [16, 17], cardiovascular diseases [18, 19], regarding its antioxidant [20, 21], and anti-inflammatory properties [22, 23]. Although a wide range of clinical studies has assessed the effects of TT on the enhancement of health [12–23], there are few randomized clinical trials on the effects of TT on athletes [24] and physically active individuals [25], and also, there is no randomized controlled trial on recreational runners. Therefore, this study has been designed to assess the efficacy of TT supplement on the nutritional, oxidative, inflammatory, and anti-inflammatory status and sports performance of recreational runners.

## Main aim

The present study is designed to determine the effect of TT supplementation on the nutritional, oxidative, inflammatory, and anti-inflammatory status and also sports performance of recreational runners.

### Primary objective

The primary objective is to assess the effect of TT supplementation on malondialdehyde (MDA), total antioxidant capacity (TAC), total oxidant status (TOS), superoxide dismutase (SOD), glutathione peroxidase (GPx), uric acid (UA), 8-iso-prostaglandin F2α (8-iso-PGF2α), protein carbonyl (PC), catalase (CAT), glutathione (GSH), nitric oxide (NO), hs-CRP, TNF-α, IL-6, IL-10, CK, LDH, MYO, muscle pain, and the aerobic and anaerobic performance of recreational runners with TT supplementation and high-intensity interval training (HIIT) training.

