### Sample size

The sample size was estimated using PASS software (version 15) based on CK changes as the primary outcome of the Ma *et al.* study. Considering the mean difference of 1128.4 units of enzyme activity per liter (U/L) between the two groups and also the SDs average of 871.05 U/L, the sample size was calculated [24]. A total of 17 recreational runners were calculated to be involved in each group with a 95% confidence level, a power of 90%, and considering the additional drop-out rate of 15%.

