#### Statistical analysis

Statistical analysis will be done using SPSS version-24 software (SPSS, Inc. Chicago, IL, USA). Regarding the missing values, the data analysis will be subjected to intention-to-treat (ITT) analysis. We will use the multiple imputation approach to perform ITT. The Kolmogorov-Smirnov test and Q–Q plot will be used to examine the normal distribution of variables. In order to compare the baseline value of quantitative and qualitative variables, the *t*-test and chi-square test will be used. To determine the change of variables at baseline and after the intervention, the paired sample *t*-test will be conducted. The mean change of the placebo and intervention group variables will also be compared using an analysis of covariances after adjusting the confounding variables. Mann-Whitney test will be used for quantitative non-normal variables. In order to compare the mean changes of the baseline and end of the trial, the paired-sample *t*-test and Wilcoxon test will be used for normal and non-normal data, respectively. Regarding repeated measured variables (three-time measurements), a two-way analysis of variance (ANOVA) with the Sidak post-hoc test will be applied to assess the time × group interactions. Also, the Mauchly sphericity test will be used to determine data homogeneity; in presence of a violation, the Greenhouse-Geisser adjustment will be used. *P* < 0.05 will be considered statistically significant in all tests. Furthermore, it is notable that in the case of non-normally distributed data, we will do Log transformations.

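### Twenty-one outcomes share primary status and each is tested at P < 0.05 with no error control across them, while the sample size supports CK only

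*Protocol article*

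**What the plan says.** **Primary objective.** It opens with "The primary objective is to assess the effect of TT supplementation on malondialdehyde (MDA), total antioxidant capacity (TAC), total oxidant status (TOS" and continues to "CK, LDH, MYO, muscle pain, and the aerobic and anaerobic performance of recreational runners". Counted out, the list is:

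- oxidative markers, 11: MDA, TAC, TOS, SOD, GPx, UA, 8-iso-PGF2α, PC, CAT, GSH, NO;
- inflammatory markers, 4: hs-CRP, TNF-α, IL-6, IL-10;
- muscle damage and pain, 4: CK, LDH, MYO, muscle pain;
- performance, 2: aerobic, anaerobic.

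That makes 21, with no ranking among them.

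**Abstract, Methods/design.** The primary outcomes are given by domain: "Changes in oxidative stress, anti/inflammatory biomarkers, and sports performance will be assessed as primary outcomes". This sentence names no muscle-damage marker, although CK, MYO and LDH appear among the abstract's blood measurements.

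**Sample size.** The calculation is "based on CK changes as the primary outcome". The sentence goes on to attribute that primary outcome to the cited study, which the Discussion describes as a study in boxers. No other outcome enters the calculation.

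**Statistical analysis.** P < 0.05 "will be considered statistically significant in all tests". For variables measured three times, "a two-way analysis of variance (ANOVA) with the Sidak post-hoc test will be applied to assess the time × group interactions".

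**The concern.** When 21 outcomes carry equal primary status and each is judged at 0.05, the error rate attached to the trial's primary claim is no longer 5%. If the supplement did nothing, the expected number of nominally significant primary results would be about one. The article does not say which outcome, or how many, must succeed, so a reader of the results would have no pre-stated basis for telling a planned finding from a chance one.

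The confidence level and power in the Sample size section describe a single CK test. They do not describe a trial with 21 primary outcomes. The abstract adds to the uncertainty, because its primary-outcome sentence leaves out the muscle-damage group to which the sizing variable belongs.

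This is not a detail left to a statistical analysis plan. The article itself fixes both the primary list and the threshold for every test.

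**Working it through.** **Inputs.** From Primary objective: 21 outcomes. From Statistical analysis: 0.05 per test (two-sided assumed, since sidedness is not stated). From Sample size: CK difference 1128.4 U/L, average SD 871.05 U/L, 95% confidence, 90% power, 15% drop-out, 17 per group. Correlations between outcomes are not given, so a range is assumed.

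**1. The plan's own figure.**
Standardised difference d = 1128.4 / 871.05 = 1.295.
Two-sample t-test, two-sided 0.05, power from the noncentral t with 2n − 2 degrees of freedom and noncentrality d·√(n/2):

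- n = 13 per group: power 0.886
- n = 14 per group: power 0.910, the first n to reach 90%

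Drop-out: 14 / (1 − 0.15) = 16.5, rounded up to 17. The stated 17 per group is reproduced. If all 17 complete, power for CK is 0.956.

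**2. Error across the 21 outcomes, independent tests.** Assume no effect on any outcome and one test per outcome.
P(at least one P < 0.05) = 1 − 0.95^21 = 0.659.
Expected number of false positives = 21 × 0.05 = 1.05. This expectation does not depend on correlation.

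**3. The same with correlated tests.** For normal test statistics with a common correlation ρ and c = 1.96:
P = 1 − ∫ φ(u) · [Φ((c − √ρ·u)/√(1−ρ)) − Φ((−c − √ρ·u)/√(1−ρ))]^21 du

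| Common ρ (assumed) | P(at least one) |
|---|---|
| 0 | 0.659 |
| 0.1 | 0.643 |
| 0.3 | 0.555 |
| 0.4 | 0.495 |
| 0.5 | 0.429 |
| 0.7 | 0.295 |
| 0.9 | 0.157 |

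The value is 0.526 at ρ = 0.35 and 0.495 at ρ = 0.4. By interpolation it crosses 50% at about ρ = 0.39.

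If outcomes are correlated only within domains (blocks of 11, 4, 4 and 2; simulation of 200,000 runs), the probability is 0.61, 0.55, 0.51, 0.46 and 0.41 at within-block correlations of 0.3, 0.5, 0.6, 0.7 and 0.8.

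**4. Reach of the Sidak step.** It is tied to the ANOVA of one variable over its three time points. It leaves the calculations in steps 2 and 3 unchanged.

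**5. One test per outcome is the lenient count.** The Statistical analysis section also plans covariance analysis or Mann-Whitney on changes, the time × group ANOVA and within-group paired tests. Counting more of these can only raise the error rate.

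**6. What keeping all 21 primary under Bonferroni would cost.** This illustrates an option that the article does not adopt. Per-test alpha = 0.05 / 21 = 0.0024. CK power at the planning values falls to 0.53 with 14 per group and 0.68 with 17. Restoring 90% would need 25 evaluable per group, and 25 / 0.85 = 29.4, so 30 per group or 60 in total.

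**The case against.** **Correlation.** Many of the markers come from the same blood samples, and the Background links oxidative stress, muscle damage and inflammation. Independence is therefore the least natural assumption. This stands. A reader might infer that a false positive primary result is more likely than not. That holds only if no outcome is affected and the common correlation is below about 0.39 (or about 0.6 within domains only), and the documents support neither condition.

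**The sizing outcome.** A reader might infer that the Sample size section names CK as this trial's sole primary outcome and so contradicts the Primary objective. It does not. It cites CK as the primary outcome of an earlier study, and CK is on the trial's own list. Sizing on one listed outcome is not a contradiction; it leaves the other 20 without a stated power.

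**The success rule.** A reader might infer that the plan declares success on any one of the 21. No such rule is written. The fair criticism is that no rule is given and the threshold is nominal.

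**Power.** CK power at 0.05 does not change because other outcomes are listed, and the Bonferroni figures describe an option not taken. Both statements are right. The figures show only that the stated size could not carry 21 primaries under that correction.

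**Choice of outcome.** The Main aim covers nutritional, oxidative and inflammatory status and sports performance, and does not mention muscle damage. Insisting on CK would alter the emphasis of the trial, so the choice should stay with the investigators.

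**The abstract.** Its sentence is a domain-level summary, so the mismatch is a wording correction and adds little weight.

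None of this supplies error control across the 21 outcomes.

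**Conclusion.** The point holds in a conditional form. The article gives 21 outcomes equal primary status, tests each at 0.05 and controls nothing across them. If the supplement has no effect on any of them and each is tested once, the chance of at least one nominally significant primary result is 66% under independence and about 55%, 43%, 30% and 16% at common correlations of 0.3, 0.5, 0.7 and 0.9. The correlations are assumptions. Even the lowest figure is about three times the nominal 5% (0.157 / 0.05 = 3.1).

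The sample size is not wrong: 17 per group follows from the stated inputs. Its 90% power refers to one CK test at two-sided 0.05 and says nothing about the other 20 primary outcomes.

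**What to change.** The Trial status section says the trial has not yet begun, although recruitment is under way, so the change can still be made in advance:

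1. Name one primary outcome, compared between groups at one stated post-intervention time point and tested at two-sided 0.05. CK is the option the existing 17 per group supports. Alternatively, name a short primary set with stated alpha control, such as Holm or a fixed sequence, and check the sample size against it.
2. Make the remaining outcomes secondary, with Holm or Benjamini-Hochberg control within families (oxidative, inflammatory, muscle damage and pain, performance), or label them exploratory.
3. State in the Sample size section that the 90% power refers to CK only.
4. Align the abstract's primary-outcome sentence with the revised Primary objective and the Sample size section.

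With CK as the single primary outcome, no extra participants, samples or measurements are needed. The price is a stricter threshold, or no confirmatory claim, for the non-primary outcomes. A different primary outcome or a primary set would need its own sample-size justification.

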### Secondary objectives

The secondary objective is to assess the effect of TT supplementation on nutritional status (energy and macronutrient intake), insulin-like growth factor-1 (IGF-1), brain-derived neurotrophic factor (BDNF), irisin, cortisol, body mass index (BMI), and body composition of recreational runners with TT supplementation and HIIT training.

## Method

### Study design and setting

This study is a double-blind, randomized, placebo-controlled trial, which will be conducted among recreational runners of Tabriz stadiums, Iran. The study protocol followed the Standard Protocol Items: Recommendations for Clinical Interventional Trials (SPIRIT) guidelines (Additional file 1, SPIRIT Checklist), and the study protocol diagram is shown in Fig. 1 [26]. Subjects will undergo two body composition analyses and three times- blood samplings. Also, written informed consent will be obtained before initiating any research procedures. The flowchart of the trial is presented in Fig. 2. The research protocol is approved by the “Ethical Committee of the Tabriz University of Medical Sciences” and registered on the “Iranian Registry of Clinical Trials” website (www.irct.ir/, IRCT20150205020965N8) and is in compliance with the declaration of Helsinki ethical principles.

**Fig. 1 Fig1:**
[figure not shown]
Study protocol diagram. TT, *Tribulus terrestris*; HIIT, high-intensity interval training; VAS, visual analog scale. -t1: 1 week pre-allocation, t0: allocation, t1: at the beginning of the study, t2: 2 weeks after the study beginning, and tx: 24 h after t2

**Fig. 2 Fig2:**
[figure not shown]
Flowchart of the trial

### Participants’ recruitment

The study population will include volunteer participants who have the eligible criteria. A total of 34 recreational runners (each group 17) will be recruited by advertisements from Tabriz stadiums, Iran. The volunteers will be screened by an initial face-to-face screening visit. In an organized meeting, participants will be provided with information, including the study procedure, requirements, possible risks, and benefits. A participant information sheet detailing study aims and requirements will be provided too.

### Eligibility

The volunteers will be included in the study if they (1) are healthy (confirmed by physical activity readiness questionnaire (PAR-Q) under the supervision of a physician [27]; (2) aged 18 to 35 years; (3) do running workouts for at least 3 days a week (240 min per week) during the last 2 years; (4) have a stable body mass during the last 5 months (changes less than 3 kg); (5) not receiving TT supplement, other antioxidants, and anti-inflammatory supplements in the last 3 months; (6) abstained from any high-intensity interval training during the last 3 months; and (7) are willing to cooperate in the study. Exclusion criteria include (1) musculoskeletal injuries; (2) smoking; (3) alcohol consumption; (4) hormone therapy; (5) long-term use of drugs and dietary supplements; (6) pregnancy; (7) lactation; (8) diabetes; (9) anemia (Hb <13g/dl); (10) cardiovascular disease; (11) infectious diseases; (12) malignancies; and (13) cognitive disorders.

### Sample size

The sample size was estimated using PASS software (version 15) based on CK changes as the primary outcome of the Ma *et al.* study. Considering the mean difference of 1128.4 units of enzyme activity per liter (U/L) between the two groups and also the SDs average of 871.05 U/L, the sample size was calculated [24]. A total of 17 recreational runners were calculated to be involved in each group with a 95% confidence level, a power of 90%, and considering the additional drop-out rate of 15%.

### Exercise protocol

This trial will use a HIIT exercise protocol as a high-intensity exercise activity designed for recreational runners using the American College of Sports Medicine (ACSM)’s physical activity recommendations [28]. The participants will do the HIIT program for two weeks (5 training sessions per week; a total of 10 sessions during the study period). A 15-min warm-up (with a variety of stretching, flexibility, walking, and running) will be included in each session. The main activity of both groups consists of two sessions with 3–4 repetitions and 30 s of running with an intensity of 90–100% of the heart rate reserve (HRR) (pressure perception 16–19) in each repetition. After each repetition and after each period, there will be 90–180 s and 2.5–4 min of active rest, respectively (active rest in the range of 40-50% of HRR) [29]. A 5-min cool-down at 45% HRR will end the training session.

### Supplementation protocol

Participants will consume the TT fruit supplement (TT, Dayan Pharma Co, Iran) or placebo (maltodextrin, Dayan Pharma Co, Iran) in random order. The supplement and placebo capsules will have perfectly the same shape, color, odor, and size. The company will code the supplement and placebo containers with different codes to keep participants and investigators blind until the end of the study. Both the TT and placebo capsules will be provided to participants weekly for two weeks. Subjects will be randomly assigned to two groups to receive 500 mg supplement or 500 mg placebo capsules, twice daily, for 2 weeks. Participants of both groups will be required to consume capsules twice daily (oral administration after breakfast and lunch) with a cup of water.

### Randomization and blinding

The recreational runners meeting the inclusion criteria will be randomized to receive either the TT (*n* = 17) or the maltodextrin capsules (*n* = 17). Randomizations will be conducted using random allocation software (RAS) via randomization blocks (Version 2.0, for Windows, Isfahan, Iran) [30]. After enrolling participants, they will be stratified into different blocks based on their VO_2max_ and gender distribution and then will be allocated to the intervention or control groups in random order. Using RAS, a random allocation sequence will be generated. Then, a third individual who is unaware of the study's aim will use computer-generated random sequences to allocate participants into TT and placebo groups.

### Adherence and compliance to the protocol of the study

There will be a one-week run-in period before study initiation. The study team will monitor participants daily during the trial, and any occurrence of adverse events will be reported. Participants will be asked to return any unused capsules to assess their level of compliance and adherence. Subjects will receive supplements every week and will be asked to bring all remaining ones of their last visit. If less than 90% of the capsules were used, the person would be excluded from the analysis. Besides, the adherence to the training program will be assessed by the number of sessions attended. If less than 90% of training sessions were attended each week, the person would be excluded.

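### Non-adherent participants are removed from an analysis that is also called intention-to-treat; the two rules conflict and the removal can bias the randomised comparison

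*Protocol article*

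**What the plan says.** All the relevant text is in the protocol article.

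- **Adherence and compliance section, capsules:** "If less than 90% of the capsules were used, the person would be excluded from the analysis".
- **Same section, training:** "If less than 90% of training sessions were attended each week, the person would be excluded". This sentence does not say whether the exclusion is from the analysis or from the study.
- **Statistical analysis section:** "Regarding the missing values, the data analysis will be subjected to intention-to-treat (ITT) analysis". The next sentence adds: "We will use the multiple imputation approach to perform ITT".

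The schedule to which the thresholds apply is "500 mg supplement or 500 mg placebo capsules, twice daily, for 2 weeks" for capsules and "5 training sessions per week; a total of 10 sessions during the study period" for training. The article defines no per-protocol set and no sensitivity analysis based on adherence. It does not say which rule governs the main analysis.

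**The concern.** An intention-to-treat analysis keeps every randomised participant in the assigned arm. The capsule rule deletes participants, including those whose outcomes were measured, because of what they did after randomisation. The result is a per-protocol analysis, and imputing missing values among those who remain does not change that.

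The deletion is unlikely to be neutral in this trial. The Background section says that hard exercise causes soreness, raised CK, LDH and myoglobin, and poorer recovery and performance. The Primary objective section lists CK, LDH, myoglobin, muscle pain and performance among the primary measures. A runner who is sore or recovering badly is a natural candidate to miss a session or stop the capsules. If the supplement works as hypothesised, this would happen more often on placebo, so exclusion would depend on outcome and on arm.

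Two things are at stake. The primary comparison could be biased in either direction. And because the plan calls the analysis intention-to-treat, a per-protocol result could be reported under that label, with the choice between the rules left open until the data have been seen.

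**Working it through.** **1. The passages side by side.** The contradiction is one of logic and needs no figure. The Statistical analysis sentence can be read in three ways.

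- *Intention-to-treat in full.* It then contradicts the capsule rule directly.
- *A statement about missing values only,* as its opening words suggest. Participants with observed outcomes are still deleted for non-adherence, so the analysis is not intention-to-treat.
- *Excluded participants are treated as missing and imputed.* This contradicts the capsule rule's statement that they leave the analysis, and it replaces outcomes that could have been measured with modelled ones.

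None of the three reconciles the sections.

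**2. The planned sample size.** Inputs from the Sample size section: CK difference 1128.4 U/L, SD 871.05 U/L, 95% confidence (two-sided assumed), power 90%, drop-out 15%.

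- Normal approximation: n = 2 × [871.05 × (1.960 + 1.282) / 1128.4]² = 12.5, so 13 per arm.
- t-test: 13.56, so 14 per arm; 14 / 0.85 = 16.5, so 17 per arm.

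The t-test version reproduces the stated 17.

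**3. How strict the thresholds are.**

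- *Capsules,* assuming one per intake: 2 × 14 = 28, and 90% of 28 is 25.2. Using 25 gives 25/28 = 89.3%, so three missed capsules exclude. If adherence is judged weekly, 90% of 14 is 12.6, and two missed capsules exclude.
- *Sessions:* four of five is 80%, so one missed session fails that week.

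The article gives no attendance rate. The table assumes independent attendance with probability p per session. It shows the share excluded by the session rule alone, under both readings of the weekly wording.

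| p (assumed) | One failed week excludes: 1 − p¹⁰ | Both weeks must fail: (1 − p⁵)² |
|---|---|---|
| 0.99 | 9.6% | 0.2% |
| 0.98 | 18.3% | 0.9% |
| 0.97 | 26.3% | 2.0% |
| 0.95 | 40.1% | 5.1% |

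Under the first reading, attendance of 98% per session already takes exclusions past the planned 15% drop-out.

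**4. Illustrative size of the bias.** Assume a normal outcome, exclusion of the 15% of one arm with the highest CK, and no exclusion in the other arm.

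- Mean of those kept, in SD units: −φ(1.036) / 0.85 = −0.274.
- In CK units: 0.274 × 871.05 = 239 U/L.
- Relative to the planning difference: 239 / 1128.4 = 21%.

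If this happens on placebo, an expected difference of 1128.4 shrinks to about 889 U/L. If it happens on the supplement, the difference grows to about 1367 U/L.

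**5. Power by number analysed per arm** (two-sided t-test, same inputs, same effect):

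| Analysed per arm | Power |
|---|---|
| 17 | 95.6% |
| 14 | 91.0% |
| 13 | 88.6% |
| 12 | 85.8% |
| 10 | 78.2% |

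Keeping everyone needs no larger sample.

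**The case against.** Several points on the other side are fair.

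- **The intention-to-treat sentence is qualified.** It opens with a reference to missing values, so it may be only a missing-data statement. That is a possible reading, but it does not rescue the plan, as shown in step 1 of the working.
- **The session rule may mean withdrawal from the study.** Withdrawal followed by imputation could fit intention-to-treat. This stands as an ambiguity, although withdrawal would create avoidable missing data. The capsule rule is explicit and is enough by itself.
- **The 239 U/L figure is an extreme case.** It needs exclusion to track CK perfectly and to occur in one arm only; equal selection in both arms with equal SDs would cancel. The 15% is the drop-out allowance, not a non-adherence rate, and in an arm of 17 it is 2.55 people. Both post-intervention samples are taken at or after the last session, so exclusion cannot select on those values directly, only through earlier soreness or recovery related to them. All of this stands, and the figure should be read as an illustration of scale.
- **Identical coded capsules, the same training in both arms, daily monitoring and a one-week run-in limit differential exclusion.** They lessen the risk. Blinding does not stop a real treatment effect from changing attendance.
- **Analysis sets are often defined in a statistical analysis plan, which is not shown.** The point here is not an omission: the article itself fixes two incompatible rules.

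**Conclusion.** The concern holds, and it should be settled before data are collected. The protocol article deletes participants on post-randomisation capsule use and also promises an intention-to-treat analysis; no reading of the text reconciles the two. The conflict decides who enters every primary comparison.

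This conclusion rests on the wording alone. The direction and size of any bias are unknown. The 21% shift depends on the one-arm, normal-outcome, perfect-selection assumptions, and the exclusion rates depend on assumed attendance. With 17 per arm, even two or three deletions in one arm could matter.

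**What to change.** - **Main analysis:** state that all randomised participants are analysed in their assigned arm, and remove the capsule-based exclusion from it.
- **Outcome collection:** obtain all three blood samples and the post-intervention tests whatever the adherence. State that failing the session threshold does not end outcome measurement.
- **Missing data:** apply multiple imputation, or a model, only to values that are truly missing.
- **Per-protocol set:** use the 90% capsule and session thresholds only to define a labelled sensitivity analysis. State whether each is judged weekly or over the two weeks, and whether one failed week is enough.

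**Cost.** A rewording of the Adherence and Statistical analysis sections, plus follow-up measurements on the few people who would otherwise be dropped. The Blood sampling section also needs a short note, because the second and third samples are timed from the last training session and someone who has stopped training has no such reference point. Non-adherers will dilute the estimate slightly. No added enrolment is needed: on the protocol's own CK inputs, 17 per arm with complete data and the same effect gives 95.6% power. The Trial status section says that the trial has not begun, so the change can be made before outcome data exist.
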